## Abstract

**Background:**

Impaired facial emotion expression recognition (FEER) has typically been considered a correlate of autism spectrum disorder (ASD). Now, the alexithymia hypothesis is suggesting that this emotion processing problem is instead related to alexithymia, which frequently co-occurs with ASD. By combining predictive coding theories of ASD and simulation theories of emotion recognition, it is suggested that facial mimicry may improve the training of FEER in ASD and alexithymia.

**Objective:**

This study aims to evaluate a novel mimicry task to improve FEER in adults with and without ASD and alexithymia. Additionally, this study will aim to determine the contributions of alexithymia and ASD to FEER ability and assess which of these 2 populations benefit from this training task.

**Methods:**

Recruitment will primarily take place through an ASD community group with emphasis put on snowball recruiting. Included will be 64 consenting adults equally divided between participants without an ASD and participants with an ASD. Participants will be screened online using the Kessler Psychological Distress Scale (K-10; cut-off score of 22), Autism Spectrum Quotient (AQ-10), and Toronto Alexithymia Scale (TAS-20) followed by a clinical interview with a provisional psychologist at the Federation University psychology clinic. The clinical interview will include assessment of ability, anxiety, and depression as well as discussion of past ASD diagnosis and confirmatory administration of the Autism Mental Status Exam (AMSE). Following the clinical interview, the participant will complete the Bermond-Vorst Alexithymia Questionnaire (BVAQ) and then undertake a baseline assessment of FEER. Consenting participants will then be assigned using a permuted blocked randomization method into either the control task condition or the mimicry task condition. A brief measure of satisfaction of the task and a debriefing session will conclude the study.

**Results:**

The study has Federation University Human Research Ethics Committee approval and is registered with the Australian New Zealand Clinical Trials. Participant recruitment is predicted to begin in the third quarter of 2021.

**Conclusions:**

This study will be the first to evaluate the use of a novel facial mimicry task condition to increase FEER in adults with ASD and alexithymia. If efficacious, this task could prove useful as a cost-effective adjunct intervention that could be used at home and thus remove barriers to entry. This study will also explore the unique effectiveness of this task in people without an ASD, with an ASD, and with alexithymia.

**Trial Registration:**

Australian New Zealand Clinical Trial Registry ACTRN12619000705189p; https://www.anzctr.org.au/Trial/Registration/TrialReview.aspx?id=377455

**International Registered Report Identifier (IRRID):**

PRR1-10.2196/24543

## Introduction

### Background

Behavioral and cognitive neuroscience has elaborated a range of emotion-related difficulties with emotion recognition [1], empathy [2], and regulation of emotions in autism spectrum disorder (ASD) [3]. However, these abnormalities are not observed in all people with ASD [4]. Traditionally, these emotion-processing difficulties have been viewed as inevitable correlates of ASD, but recent research suggests that their presence is variable and better explained by co-occurring alexithymia. This suggestion is termed the alexithymia hypothesis [5] and is gaining significant support [6]. Alexithymia is a personality construct that relates to the inability to distinguish or describe the subjective feelings in the body produced by emotion. Alexithymia is related to both empathy [7] and emotion recognition [8] deficits. Severe degrees of alexithymia are manifested in up to 65% of adults with ASD [9].

The 2 forms of alexithymia, type 1 and type 2 [10], differ on the affective and cognitive dimensions [11]. Type 1 alexithymia includes high levels of both dimensions, whereas type 2 alexithymia only includes high levels of the cognitive dimension. Type 1 relates to reduced emotional reactivity (or a severe downregulation of emotional experience), and type 2 is typical emotional reactivity, but a reduced ability to interpret and describe that emotion [12].

### Simulation Theories

Simulation theories [13] may explain how these emotion processing deficits occur in alexithymia. Simulation theories refer to the perception of a facial expression triggering a simulation of that expression's corresponding emotion within the perceiver. This simulation is then used to understand the perceived facial expression meaning to facilitate emotion recognition and empathy [14,15].

Alexithymia can explain the failure of this simulation process. Studies suggest that reduced emotion recognition accuracy in alexithymia is related to reduced activity in the insula (a small region within the cerebral cortex) [16]. The insula is related to the cognitive processing of emotions and generation of emotions [17,18], which are both required for simulation to work. The insula has also been noted as a critical relay station between the action representation system, which represents the vision of facial expressions, and limbic areas, which generate emotion [19]. In alexithymia, it has been found that the insula is hypoactive [12]. Therefore, when a facial expression is seen, the insula may fail to relay this information to the limbic area, which typically simulates the observed emotion.

The simulation process may also fail in alexithymia due to an inability to access the emotional information generated by a simulation. There are 2 explanations as to why people with alexithymia may not be able to access the simulation information. The first explanation is because of the inability to describe emotions in the self and differentiate them from bodily sensations, which is the hallmark of alexithymia [20]. Second, significant interoceptive deficits have been observed in alexithymia, which explains why people with alexithymia cannot accurately assess their current emotional state [21,22]. This interoceptive deficit would suggest that, even if an emotion was generated during simulation, people with alexithymia would not be able to appraise and understand this simulated emotion. Therefore, the simulation process would not provide any information about what the other person is feeling.

Another way that alexithymia may explain a failure of the simulation process is if people with alexithymia have trouble assigning the simulated emotion as belonging to the “sender” of the emotional expression [23], which is termed self-other distinction. If an emotion is simulated, but not tagged as belonging to the “sender,” then the simulation cannot aid recognition of the sender's emotion.

While alexithymia is a key element in explaining the failure of this simulation process, it does not provide a finer mechanistic explanation. However, theories proposed within predictive coding frameworks (PCFs) are beginning to provide a compelling explanation.

### Predictive Coding Frameworks, Interoception, and Self-Other Distinction

PCFs suggest that the brain uses complex mathematical models to predict the most likely truths occurring in ourselves and our worlds [24,25]. These models are continually updating to increase efficiency and accuracy at explaining the most probable cause of sensory inputs [24]. Quattrocki and Friston [26] proposed a PCF theory that suggests that the causal factor of ASD is an aberrant oxytocin system. They proposed that the neuropeptide oxytocin has 2 functions. First, it has a role in prescribing the perceived accuracy of an interoceptive signal within the body. The perceived accuracy of an interoceptive signal is important because, if a top-down prediction and bottom-up stimulus do not match up, the brain will rely more heavily on the information source it perceives to be most accurate.

Therefore, when generating a model of the current state of the self or body, oxytocin mediates how much weight will be given to an interoceptive stimulus versus predictive models of the body’s current state. Second, oxytocin has a role in enabling the plasticity required for the brain to generate a model of the emotional and social “self.” Without these models, an over reliance would be put on bottom-up information, as described by Pellicano and Burr [27].

Two constructs implicated in forming a distinction between the self and others were introduced in the earlier paragraphs: interoception and the self. Interoception is the perception of one’s own internal state, including the perception of sensations such as thirst, stress, temperature, sleepiness, and heartbeat. One use of these sensations is for inferring emotional states and generating a model of the embodied “self” [25]. The embodied “self” is the physical body belonging to an individual, which the brain distinguishes as separate from other matter in the environment [28]. These bottom-up stimuli inform limbic brain regions and are suggested to assimilate with higher-order models of the self in the insula, anterior cingulate cortex, and ventromedial prefrontal cortices [29,30]. Therefore, these 3 areas are responsible for producing top-down predictions of perceptual information that has an emotional valence (ie, “gut feelings”). These emotionally valenced predictions are key components of the subjective emotional experience and self-awareness [25]. Quattrocki and Friston [26] suggested that one way in which models of the self can be weak is due to an aberrant oxytocin system. They suggest that an aberrant oxytocin system results in a failure to attribute less accuracy to interoceptive cues, which leads to a biased use of interoceptive cues over top-down prediction models. This biased use of interoceptive cues results in the models of the self being underdeveloped, lacking efficiency and accuracy. Underdeveloped models of the self make the ability to form a self-other distinction exceedingly difficult, and therefore, the ability to attribute an emotion to another person is compromised. Consequently, any emotional presentation generated via simulation for either empathy or emotion recognition may be experienced, however, not able to be attributed to the other person.

### Facial Mimicry and Oxytocin

Facial mimicry and oxytocin may aid these interoceptive and emotional processing symptoms. Aoki and colleagues [31] showed that activity in the insula could be increased during emotion recognition tasks in people with ASD. They found that oxytocin significantly increased emotion recognition (*P*=.043) and increased activity in the insula during these tasks (*P*=.004). This study did not measure alexithymia; however, emotion recognition deficits in ASD have been found to become insignificant after accounting for alexithymia [32]. Therefore, this relationship between emotion recognition, oxytocin, and activity in the insula may actually be more applicable to alexithymia than to ASD.

One natural way to increase oxytocin has been suggested by Delaveau et al [33] by using mimicry. Mimicry referrers to copying the movements of another person. Delaveau et al [33] found that when mimicking and being mimicked, there was increased activity in the insula, similar to the results of Aoki and colleagues [31]. Paired with prior behavioral studies [34], the authors suggested that these results may be due to mimicry increasing the salience of social cues through the modulation of brain regions related to self-other processing. Further, they suggested that the systematic use of mimicry may provide therapeutic benefits. Given that both oxytocin and self-other processing have been implicated as key targets for the emotional processing problems observed in alexithymia, an intervention that includes mimicry may be a novel and simple therapeutic method.

Lewis and Dunn [35] offered support for the effectiveness of instructed mimicry in their emotion recognition study. They found that instructions to mimic a facial expression improved the recognition of that emotional expression selectively for people with high autistic traits. This finding was similar to that of Luminet et al [36] who found that oxytocin selectively benefits people high in alexithymia on a similar task. Additionally, other studies have shown that by restricting facial mimicry, facial emotion expression recognition (FEER) decreases (eg, [37-39]).

### Study Aims

The first aim of this study is to evaluate the efficacy of an instructed mimicry task condition to improve FEER compared to a control condition and also from baseline to posttest in adults with and without alexithymia and ASD. The second aim of the study is to confirm findings by Cook et al [32] that FEER is related to alexithymia and not ASD. As an ancillary aim, the study will also collect data for further research on how eye-gaze patterns in type 1 alexithymia and type 2 alexithymia uniquely relate to FEER in the same sample.

## Methods

### Study Design

The study design is a mixed factor 2x2x2 within-between design. Participants who meet inclusion and exclusion criteria will be randomized to a control task or the experimental task. Inclusion and exclusion criteria and pretrial control variables will be collected during an online screening stage and during an in-person clinical interview. Baseline outcomes will be assessed directly before the control task or experimental task. They will then be assessed again during the control and experimental tasks. The study will conclude with a brief measure of satisfaction of the task and a debriefing session. See Multimedia Appendix 1 for a step-by-step workflow of a participant through the study.

### Participants

We will recruit through local ASD support groups, online social media, and noticeboard advertisements (eg, at Federation University Australia). We will also use snowball recruiting to better penetrate the ASD community. Participants with an ASD (based on the assessments described in the Assessment section) will be assigned to the ASD group. Other participants will be assigned to the alexithymia-matched general population group (AM group).

The researchers will also use the 20-item Toronto Alexithymia Scale (TAS-20) total scores [40] to match the ASD group with the AM group without an ASD. Specifically, the number of participants in each group meeting criteria for alexithymia will be matched as indicated by TAS-20 scores ≥61, which is how groups have been matched in similar studies (eg, [32]).

The inclusion criterion is that participants are 18 years of age and older. The ASD group also has the added inclusion criterion of a confirmed ASD based on the assessment described in the Assessment section. Exclusion criteria include the participant having another mental health condition (other than an ASD if in the ASD group) diagnosed by a clinician and that the Kessler Psychological Distress Scale (K10) [41] indicates a significant level of distress (cut-off score of 22).

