### Assessments

The main aim of the current study is to assess the efficacy of the intervention in the general population and an ASD population, but also if people with high levels of alexithymia gain additional benefit. Further, this study will aim to replicate the study by Cook et al [32], which suggested that alexithymia, not ASD, predicts poor FEER. This requires having a general population group and another group with people with ASD, with both groups being matched on levels of alexithymia. Therefore, participants will be prescreened online to facilitate creating this composition of participants. During the online screening stage, participants will choose to consent in the study, complete the TAS-20, and indicate if they have an ASD or if they have been diagnosed with an ASD. During this screening stage, participants will also complete demographic information, the Autism Spectrum Quotient (AQ-10) [42], and the K-10.

Participants will then be invited to a clinical interview with a provisional psychologist (PP) at the Federation University Psychology Clinic who will confirm a reported diagnosis of ASD and complete an observational assessment that gives a diagnostic indication of an ASD. Participants who have reported a diagnosis will be asked what instrument was used and if the PP can request a copy of the results. The PP will also complete the Autism Mental Status Exam 2.2 (AMSE) [43,44]. The AMSE is an 8-item observational assessment that takes place during a clinical interview and predicts ASD classification on the Autism Diagnostic Observation Schedule (ADOS) [45]. During this clinical interview, participants will also be administered the Depression Anxiety Stress Scales-21 (DASS-21) [46] and the Wechsler Abbreviated Scale of Intelligence (WASI-II) [47] to assess depression, anxiety, and IQ, which will be used as control variables in the analyses of the results.

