### Assessor Training and Supervision

The PPs will have pre-existing training in conducting clinical interviews, including mental status examination, as well as administration of symptom measures and cognitive testing. They will be supervised by approved supervisors and endorsed clinical psychologists with extensive clinical experience (at least 10 years) working with and diagnosing people who have an ASD. All psychologists will participate in the AMSE training [48], which entails working through the AMSE manual, examples, and posttests. The viewing, rating, and discussion of additional videos of adults with ASD will enhance interrater reliability and ensure understanding of diagnostic criteria.

Clinical interviews will be recorded, and AMSE scoring decisions will be made with one or, where it is difficult to reach consensus, both of the supervisors. Participants who meet AMSE criteria and have a confirmed historical diagnosis will be included in the ASD group.

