#### AMSE

The AMSE 2.2 [43] is an 8-item clinician observational assessment that aims to structure the documentation and observation of social, communicative, and behavioral function in people with ASD. The AMSE takes place during a clinical interview without adding extra work or time during the examination. Scores higher than 4 predict ADOS [53] classification with a sensitivity of 94% and specificity of 81% [44]. Interrater agreement is high at 0.97, and internal consistency was fair with a Cronbach α of .72 [43].

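### The AM group is whoever fails a two-part ASD rule, so people with self-identified or undiagnosed ASD can enter the non-ASD comparator and pull the ASD–AM contrast toward the hypothesised null

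*Protocol article*

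**What the plan says.** Assessor Training and Supervision sets a two-part rule for the ASD group: "Participants who meet AMSE criteria and have a confirmed historical diagnosis will be included in the ASD group". Participants makes the comparator the remainder: "Other participants will be assigned to the alexithymia-matched general population group (AM group"). The same section describes the purpose of the TAS-20 as "to match the ASD group with the AM group without an ASD", and the Abstract describes the sample as "equally divided between participants without an ASD and participants with an ASD".

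Three other statements bear on who reaches the AM group:

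- The exclusion criteria in Participants remove anyone with "another mental health condition (other than an ASD if in the ASD group) diagnosed by a clinician".
- At online screening (Assessments), volunteers "indicate if they have an ASD or if they have been diagnosed with an ASD". These are two separate possibilities.
- On recruitment, Participants adds to local ASD support groups: "We will also use snowball recruiting to better penetrate the ASD community".

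Table 1 lists the AMSE and the AQ-10 under eligibility, but the text gives no rule that uses either to keep a person out of AM.

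**The concern.** A group described as having no ASD is filled by a rule that tests only for failure to qualify as ASD. With a two-part ASD rule, failing either part is enough to leave the ASD group, and the article's default destination is then AM. Two kinds of volunteer pass through with no exclusion that reaches them: people who regard themselves as having an ASD but have no diagnosis, and people who are AMSE-positive without a diagnosis.

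The second aim is to confirm that FEER relates to alexithymia and not to ASD. Two of the hypotheses predict no significant ASD–AM difference, one at baseline and one in improvement. Any true ASD cases in AM make the groups more alike, so the error favours the predicted result. A non-significant ASD–AM difference could then reflect the composition of the comparator as well as the alexithymia hypothesis, and the data would not separate the two.

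**Working it through.** **1. Where each type of volunteer goes under the stated rules**

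| Volunteer | ASD group? | Caught by an exclusion? | Destination as written |
|---|---|---|---|
| Confirmed diagnosis, AMSE-positive | Yes | No (exempted) | ASD |
| Confirmed diagnosis, AMSE-negative | No | Apparently yes: the ASD exemption covers only the ASD group | Excluded, though the residual rule says AM |
| Reported diagnosis that cannot be confirmed | No | Unclear whether a report counts as clinician-diagnosed | Unclear: AM or excluded |
| No diagnosis, says they have an ASD | No | No | AM |
| No diagnosis, AMSE-positive | No | No | AM |
| No diagnosis, AMSE-negative, no self-report | No | No | AM, as intended |

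Rows four and five are the defect. Rows two and three are wording that must be reconciled.

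**2. The plan's own sample size**

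Inputs from Sample Size Calculation: f² = 0.27, alpha 0.05, power 80%, N = 58, raised to 64 for 10% attrition. An omnibus regression F test with the six predictors of Table 3 (noncentrality f² × N) gives N = 58, with power 0.808, so the 58 reproduces. For attrition, 58 × 1.10 = 63.8, which gives 64. Half of 58 is 29 per group and half of 64 is 32.

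**3. Dilution**

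Let c be the share of AM who truly have an ASD. If those people score like the ASD group, the expected ASD–AM difference is d(1 − c), where d is the true difference in SD units. The article does not give c, and it does not give d for this contrast. I assume c from 0 to 30% and d = 0.5, with a two-sided 5% t test and 29 per group (noncentral t, 56 degrees of freedom, noncentrality d(1 − c)√(29/2)):

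| c | d(1 − c) | Power |
|---|---|---|
| 0 | 0.50 | 46.5% |
| 10% | 0.45 | 39.2% |
| 20% | 0.40 | 32.2% |
| 30% | 0.35 | 25.8% |

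Mixing two populations in AM also widens its spread slightly. Dividing by √(1 + c(1 − c)d²/2) gives 38.8%, 31.7% and 25.3% in the last three rows, so the refinement hardly matters.

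The pattern does not depend on starting from low power. With 32 per group and an assumed d of 0.72, using the same refinement, power is 81% at c = 0, 71% at 10%, 60% at 20% and 49% at 30%.

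If Autism in Table 3 is entered as group membership, which the article does not say, its coefficient shrinks by about the same factor.

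**4. How many undiagnosed AMSE-positive people truly have an ASD**

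Using the AMSE figures ("sensitivity of 94% and specificity of 81"%) and an assumed 10% true prevalence among undiagnosed volunteers: true positives 0.94 × 0.10 = 0.094; false positives 0.19 × 0.90 = 0.171; share truly ASD 0.094/(0.094 + 0.171) = 35%. At 2% prevalence: 0.0188/(0.0188 + 0.1862) = 9%. So c is well below the AMSE-positive share of AM unless prevalence among these volunteers is high.

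**The case against.** The strongest reply is that the exclusion criterion already does the work. Because ASD is exempted only for members of the ASD group, a clinician-diagnosed person outside that group is excluded and does not become a control. This stands. A reader might infer that diagnosed but AMSE-negative people become AM controls, and might use the 94% sensitivity to put this at about 2 of every 34 diagnosed volunteers (34 × 0.06 = 2.04). The documents do not support that. Read literally, the exclusion removes these people, and the sensitivity is quoted against ADOS classification, not historical diagnosis.

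The remaining arguments stand in part:

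- Many undiagnosed AMSE-positive people would be false positives, as step 4 shows, so they cannot all be counted as ASD cases. This limits c but does not make it zero, and it says nothing about people who identify themselves as having an ASD.
- The intent that AM be free of ASD is explicit. But the intent is a description, and the stated allocation rule does not deliver it.
- The participant flow diagram and the workflow appendix are not in the copy reviewed and may route discordant cases. If they do, the text should say the same.
- The first aim, mimicry against control, is a randomised comparison with both groups represented in each arm. Misclassification between ASD and AM does not bias it. This stands in full and limits the scope of the point.

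**Conclusion.** The point holds for the ASD–AM comparison and for the autism term in the regression. AM is a residual group with no positive no-ASD criterion, and self-identified or AMSE-positive people without a diagnosis enter it under the rules as written. The direction, toward the hypothesised absence of a difference, does not depend on c provided misplaced cases resemble the ASD group. The size does depend on c: about a (1 − c) shrinkage, so one tenth of the contrast is lost at c = 10% and three tenths at c = 30%. That range and the true differences used are assumptions, and the documents fix neither.

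The handling of diagnosed people who miss the ASD group is a conflict in the text, not a demonstrated source of contamination. Nor do the documents support a wider inference that the efficacy result is compromised. This is a flaw in a stated rule that serves the second aim, and the rule can be corrected before the first participant is enrolled.

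**What to change.** 1. In Participants, replace the residual assignment with a positive criterion for AM: no self-reported, suspected or diagnosed ASD at online screening or clinical interview.
2. Reconcile this with the exclusion criterion, so that one sentence states what happens to a person with a clinician diagnosis who does not meet the ASD-group rule.
3. State that people with a reported but unconfirmed diagnosis do not enter the ASD–AM comparison.
4. Prespecify a sensitivity analysis of the ASD–AM contrasts (baseline and improvement) and of the autism regression term that omits AM participants who are AMSE-positive without a diagnosis.

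Omitting AMSE-positive controls belongs in the sensitivity analysis and not in the main definition. At 81% specificity, up to about 19% of true non-ASD controls would be AMSE-positive. Removing them could leave a comparator with unusually few autistic traits and so inflate the contrast.

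The cost is a few sentences and some volunteers lost to the group comparison. The self-report and the AMSE are already collected, and the Timeline section says recruitment had not begun as of June 2021. After enrolment the groups could only be redefined post hoc.
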